## Abstract

**Introduction:**

Wolfram syndrome (*WFS1-*Spectrum Disorder) is an ultra-rare monogenic form of progressive neurodegeneration and diabetes mellitus. In common with most rare diseases, there are no therapies to slow or stop disease progression. Sodium valproate, an anticonvulsant with neuroprotective properties, is anticipated to mediate its effect via alteration of cell cycle kinetics, increases in p21^cip1^ expression levels and reduction in apoptosis and increase in Wolframin protein expression. To date, there have been no multicentre randomised controlled trials investigating the efficacy of treatments for neurodegeneration in patients with Wolfram syndrome.

**Methods and analysis:**

TREATWOLFRAM is an international, multicentre, double-blind, placebo-controlled, randomised clinical trial designed to investigate whether 36-month treatment with up to 40 mg/kg/day of sodium valproate will slow the rate of loss of visual acuity as a biomarker for neurodegeneration in patients with Wolfram syndrome. Patients who satisfied the eligibility criteria were randomly assigned (2:1) to receive two times per day oral gastro-resistant sodium valproate tablets up to a maximum dose of 800 mg 12 hourly or sodium valproate-matched placebo. Using hierarchical repeated measures analyses with a 5% significance level, 80% power and accounting for an estimated 15% missing data rate, a sample size of 70 was set. The primary outcome measure, visual acuity, will be centrally reviewed and analysed on an intention-to-treat population.

**Ethics and dissemination:**

The protocol was approved by the National Research Ethics Service (West of Scotland; 18/WS/0020) and by the Medicines and Healthcare products Regulatory Agency. Recruitment into TREATWOLFRAM started in January 2019 and ended in November 2021. The treatment follow-up of TREATWOLFRAM participants is ongoing and due to finish in November 2024. Updates on trial progress are disseminated via Wolfram Syndrome UK quarterly newsletters and at family conferences for patient support groups. The findings of this trial will be disseminated through peer-reviewed publications and international presentations.

**Trial registration number:**

NCT03717909.

STRENGTHS AND LIMITATIONS OF THIS STUDYThis study has been designed as a ‘gold standard’ double-masked international multicentre randomised controlled trial, to provide robust evidence for the effectiveness or otherwise of the intervention.The Pivotal Trial design allowed incorporation of all data required for a future marketing authorisation application should the trial demonstrate efficacy.Patient support groups from four countries chose the primary outcome measure (visual acuity) as the highest priority for affected people and their carers.The trial does not include children under 6 years, or adults for whom vision has already been lost.

## Introduction

 Wolfram syndrome is a rare combination of neurodegeneration and diabetes, with an estimated prevalence of 1:500 000.^1^ The minimum clinical diagnostic criteria include both diabetes mellitus and progressive optic atrophy in childhood.^2^ It shows primarily autosomal recessive inheritance, due to mutations in the gene *WFS1*.^3 4^ Approximately 50% of affected children develop signs of neurodegeneration such as cerebellar ataxia and brainstem function impairment by 15 years of age^5^; and severe vision impairment by 18 years.^6^ Up to two-thirds of affected people develop cranial diabetes insipidus, sensorineural deafness and neurogenic bladder; other complications include hypogonadism in males, neurological and psychiatric disorders.^2^ There is currently no specific treatment for this progressive disorder.

The protein*,* Wolframin, negatively regulates endoplasmic reticulum (ER) stress through suppression of ATF6 signalling,^7^ maintenance of ER calcium homeostasis,^8^ cell cycle progression^9^ and granular acidification.^10^ Depletion of Wolframin expression and/or activity results in cell death. A potent cyclin-dependent kinase inhibitor, p21^cip1^, functions as a regulator of cell cycle progression at the G1 and S phase.^11^ It inhibits the apoptosis induced by cell cycle arrest and p53 expression. We observed significant p21^cip1^ downregulation in three Wolframin-depleted cell lines at baseline; however, the expression of p21^cip1^ was associated with inhibition of progression through the G2 phase of the cell cycle and prevention of neuronal apoptosis.^12^

p21^cip1^ has been proposed as a potential therapeutic agent that produces functional regeneration following central nervous system injuries.^13^ It is also known to induce/promote synaptogenesis and the survival of new neurons.^14 15^ Its expression can be increased by known drugs (high content screen of 1040 US Food and Drug Administration (FDA)-approved drugs carried out by [name] *et al*, University of Birmingham; unpublished). Based on these findings, a panel of 22 drugs was screened that are known to increase expression of p21^cip1^, that cross the blood-brain barrier and that have a reasonable side effect profile. Sodium valproate (VPA) was selected based on: a well-established safety profile; decades of use as a licensed medicine in children; freedom to operate; and European Medicines Agency (EMA) (EU/3/14/1428) and FDA (08/05/2015) Orphan Drug Designation 2015: sodium VPA for the treatment of Wolfram syndrome; Core Technology Patent WO2014049366).

VPA is currently approved for the treatment of epilepsy and bipolar disorder and potentiates the inhibitory action of gamma amino-butyric acid (GABA) through an action on the further synthesis or further metabolism of GABA.

Our hypothesis is that VPA-induced p21^cip1^ expression may prevent neuronal death through its ability to halt re-entry of neurons into the cell cycle, or arrest progression through the G1/S checkpoint, allowing neuronal survival. Our aim is that treatment with VPA will slow the progression of neurodegeneration in patients with Wolfram syndrome.

### Trial design overview

TREATWOLFRAM is a multicentre, double-blind, placebo-controlled randomised clinical trial of treatment for 36 months with VPA as 200 mg gastro-resistant tablets, for children and adults with Wolfram syndrome confirmed by at least one pathogenic mutation in the Wolfram gene. The primary aim is to determine the efficacy of VPA compared with placebo in slowing the rate of deterioration of VA. Eligible participants are randomly assigned by the clinical trials unit to once-daily or twice-daily treatment with either VPA or VPA-matched placebo (control) in a 2:1 ratio (VPA:placebo). A schematic of the trial design is summarised in figure 1.

**Figure 1 F1:**
[figure not shown]
Schematic of sodium valproate efficacy and safety in Wolfram syndrome trial design. Eligible participants are randomly assigned to a 36-month treatment of once-daily or twice-daily sodium valproate or placebo control. Both the trial investigators and the participants are blinded to drug allocation. ETDRS, early treatment diabetic retinopathy study chart; TC, telephone call; V, visit; VA, visual acuity assessment; W, week.

The Standard Protocol Items: Recommendations for Intervention Trials checklist^18^ is provided as online supplemental appendix 1 and WHO Trial Registration Data Set in online supplemental appendix 2.

### Patient selection

Eligible children and adults (6 years old and above) are identified and invited to participate at the participating trial site centres in the UK (Queen Elizabeth University Hospital, Birmingham Women’s and Children’s Hospital), and internationally, Servicio Andaluz de Salud de la Consejería de Salud y Familias in Almeria, Spain; Medical University of Lodz, Poland; Hôpital Européen Georges Pompidou and Assistance Publique Hôpitaux de Paris, France; and CHU Gui de Chauliac, Montpellier, France.

### Consent

It is the responsibility of the local principal investigator to obtain written informed consent from each participant, and for paediatric participants, obtain the participant’s parent/legal guardian consent, with every reasonable effort to obtain a child’s assent, prior to performing any trial-related procedure. Age-specific participant information sheets and parent/legal guardian information sheets are available from the trials office ([contact]) as well as age-specific and parent/guardian-specific informed consent forms. Example adult participant information sheets and consent forms are included in onlinesupplemental appendices 3  4, respectively.

### Participant pathway

The TREATWOLFRAM trial involves 11 participant-related visits at their nearest trial site as follows: (1) screening, enrolment, baseline investigations and randomisation (visit 1); (2) dose escalation and safety visits (visits 2, 3); (3) dose maintenance (visits 4–11, up to 156 weeks post randomisation); and (4) post-treatment follow-up (telephone call 4 weeks after cessation of treatment). The schedule of trial visits and data collection is summarised in online supplemental appendix 5.

### Treatment groups

#### Sodium valproate (active experimental group)

Sodium VPA 200 mg gastro-resistant tablets, containing the active substance VPA, ATC code N03AG01, is supplied by Wockhardt UK. This is packaged and labelled in accordance with EMA regulations on Good Manufacturing Practice.

#### Sodium valproate-matched placebo (inactive, placebo-control group)

Placebo is packaged, labelled and distributed by a third party mirroring that of VPA. Placebo is identical in appearance to VPA 200 mg gastro-resistant tablets.

### Dose modifications

VPA treatment commences at a dose based on the participant’s body weight (10 mg/kg/day in one or two divided doses) and increases in 200 mg or 400 mg increments over 4 weeks to 40 mg/kg/day or a maximum of 800 mg/day for participants aged between 6 years and less than 12 years, or a maximum of 1600 mg/day for those aged 12 and over. For daily doses of 400 mg or more, the doses are given as two divided doses 12 hours apart. Participants then remain on this dose until the end of the trial, unless adverse events are experienced.

In the event of a moderate adverse event (AE) that is possibly related to the Investigational Medicinal Product (IMP), participants are assessed and their daily dose of IMP reduced by 200 mg increments or more per week for adults until tolerated; or by 10 mg/kg increments per week for children. Participants are then asked to continue on the lower dose to the end of the trial unless, in the opinion of the local investigator, a higher dose is likely to be tolerated. If a participant has temporarily discontinued treatment, they may also be allowed to restart treatment, provided that:

The participant stopped IMP for less than 180 days (both continuously and cumulatively).The AE(s) that prompted the dose reduction or cessation have resolved.If the AEs included abnormal blood investigations such as liver function tests, these have returned to the normal range.

### Concomitant therapy

All concomitant medications given in relation to standard clinical management are recorded for this trial via the electronic case report form database. Within the summary of product characteristics (SmPC) is an extensive list of drugs that can interact with VPA. Prohibited concomitant medications and those to be used with caution are listed in online supplemental appendix 6.

In addition to trial medications, participants continue to receive standard national care recommendations concerning diabetes mellitus (ie, glucose-lowering agents) and other coexisting illnesses throughout the trial. All participants follow their national pregnancy prevention programmes for patients taking VPA. The use of VPA in pregnancy is associated with a teratogenic risk to the fetus. Therefore, an inclusion criterion was that all women of childbearing potential must use a highly effective method of contraception, without interruption, for the whole of the IMP period.

### Treatment compliance

Treatment compliance is monitored by a review of the numbers of returned tablets in the used tablet containers and the participants’ self-completed treatment medication diaries. The latter provide written evidence of dosage, time and date when each participant administers the study drug. For all participants, plasma VPA levels are measured at baseline, day 42, day 360, day 720 and day 1080 in an independent central laboratory in Birmingham (UK). Results are provided every 6 months to the trial statistician, who then sends a report to the Data Monitoring Committee.

### Outcome measures

#### Primary outcome measure

The primary outcome measure is the rate of change in VA as assessed by corrected VA in each eye, measured on the Logarithm of the Minimum Angle of Resolution (LogMAR) scale using Early Treatment Diabetic Retinopathy Study (ETDRS) charts. The VA is calculated by testing each eye independently using the patient’s own refractive correction (glasses or contact lenses), as required. Increases in LogMAR represent deterioration. Due to the potential for assessor error, completed ETDRS charts are sent to an independent central reviewer who reviews calculations. VA is assessed at screening, and then at day 0 (baseline), 180, 360, 540, 720, 900 and 1080.

#### Secondary outcome measures

Safety, measured by adverse events according to the National Cancer Institute’s (NCI) Common Terminology Criteria for Adverse Events (CTCAE) V.4.0.^19^Tolerability, measured by dose achieved, days of treatment and treatment-related dose reductions and discontinuations.Pons volume (PV), a surrogate marker for neurodegeneration, measured in mm^3^, estimated from standardised analysis of MRI of the brain.Brainstem and brainstem substructure volumes, measured by MRI.Peripapillary retinal nerve fibre thickness, measured by optical coherence tomography.Colour vision measured by Hardy Rand and Rittler test of Isihara plates.^20^Contrast sensitivity, if available.Comprehensive ophthalmic examinations included slit-lamp assessment of the anterior and posterior segment, documentation of pupil examination and eye movement examination including strabismus and nystagmus.Sleep, measured by questionnaires (described in the Questionnaires subsection).Balance, measured by Mini-Balance Evaluation Systems Test (Mini-BESTest).^21^Hearing, measured by pure tone audiometry.Wolfram Unified Rating Scale.^22^Mood, measured by the KIDSCREEN questionnaire.^23^Quality of life, measured by questionnaires (described in the section below).Pancreatic beta cell reserve, measured by mixed meal tolerance test or equivalent (UK participants only, optional).

### Analytical methods

#### Brain imaging

MRI assessments are conducted at screening (day −28); month 12 visit (day 360); month 24 visit (day 720); and month 36 visit (day 1080). While there is some flexibility between centres, all longitudinal scan sequences on an individual participant must be identical with regards to head coil choice, scanner make and model, field strength and scan parameters.

The T1-weighted volume scan is segmented centrally by the imaging team to estimate the volume of the whole brain stem, brainstem substructures and specifically PV. Global and regional brain volumes will also be measured to disambiguate any brainstem changes with global growth or atrophy. The T2-weighted volume scan sequence enables clinical reporting of the scans to assess the safety of VPA in participants. Additionally, the T2-weighted volume assists in the calculation of total intracranial volume, needed to normalise the brainstem and PV measurements.

#### Clinical and laboratory data

Biochemistry assessments include blood (serum or plasma) urea, creatinine, electrolytes (sodium, potassium), bone chemistry (plasma calcium, phosphate, alkaline phosphatase, vitamin D, parathyroid hormone), lactate, random glucose, random plasma osmolarity and urine osmolarity, glycated haemoglobin, liver function tests (total bilirubin, alanine transaminase, aspartate transaminase, gamma glutamyl transferase), coagulation (prothrombin time, thrombin time, activated partial thromboplastin time, international normalised ratio, fibrinogen), ammonia, amylase. Haematology assessments include haemoglobin, white count and differential, platelet count. Thyroid function tests (TFT) will include thyroid-stimulating hormone, free triiodothyronine and free thyroxine. TFT are performed at baseline (visit 1), day 90 (visit 5), day 360 (visit 7), day 720 (visit 9) and day 1080 (visit 11).

#### Questionnaires

The following questionnaires are used in this trial:

International Consultation on Incontinence Questionnaires (ICIQ): ICIQ Female Lower Urinary Tract Symptoms,^24^ ICIQ Male Lower Tract Symptoms^25^ and ICIQ Paediatric Lower Urinary Tract Symptoms (CLUTS both self-administration and caregiver reported).^26^Quality of life questionnaires: Pediatric Quality of Life Inventory (child 8–12, parent of child 8–12, teen 13–18, parent of teen 13–18).^27^Sleep questionnaires: Sleep-related Breathing Disorder scale extracted from the Paediatric Sleep Questionnaire (referred to as PSQ) parent report for those under 18^28^ and Pittsburgh Sleep Quality Index self-report.^29^Visual function questionnaires: Vision-related Quality of Life for Children (for patients aged 8–12 years), Vision-related Quality of Life for Young People (for patients aged 12–18 years),^30^ Functional Vision Questionnaire for Children (for patients aged between 8 and 12 years), Functional Vision Questionnaire for Young People (for patients aged 13–18 years)^31^ and the 25-item Visual Function Questionnaire (both self-report or interviewer-administered for adults).^32^Mood questionnaires: KIDSCREEN (patients aged 8–18)^33^ and Hospital Anxiety and Depression Score (adults).^34^

For non-UK sites, questionnaires were administered only if there was a validated translated version available in the country.

### Statistical analysis

#### Sample size

The target sample size for this trial is pragmatic, driven by what is required to conduct a rigorous scientific trial and what is feasible. Using hierarchical repeated measures analyses with a 5% significance level, 80% power and accounting for an estimated 15% missing data rate, the total sample size is 70, to be recruited over all sites with no one site recruiting more than 50% of all participants. The methods of Diggle *et al* were used for the sample size calculation.^35^

A longitudinal hierarchical model analysis for VA has been chosen because: (1) Wolfram syndrome symptoms progress gradually over years; (2) a repeated measures analysis yields a feasible sample size.

We used data on a cohort of 26 patients with Wolfram syndrome, kindly provided by [name] (St Louis Wolfram Research Clinic, USA). Our calculation assumed:

Mean progression of VA loss under placebo patients was 0.082 LogMAR units per annum (p.a.).The effect of being on active treatment resulting in an effect size of 0.041 p.a. (representing a halving of the rate of progression).Homoscedastic errors distributed N (0, 0.074^2^).Random gradients N (0, $\sigma_{B}$). In the St Louis cohort data, we noted that a rapidly progressing patient inflated the estimate of $\sigma_{B}$. This patient was measured using off-chart methods, which will not be used in the primary analysis of TREATWOLFRAM. Initially, we estimated $\sigma_{B}$ to be 0.036, the estimate obtained by fitting the model to the St Louis data, excluding the patient with off-chart measurements. We assessed sensitivity to this figure (by including observations from this patient) in our simulation study.That VA LogMAR scores at baseline range from 0 to 1.6 to reflect the patients that will be recruited in the trial (VA greater than 1.6 is an exclusion criterion).

We expect that some participants will discontinue early, leading to less than 100% data collection for the primary outcome. We assume that participants provide data until they discontinue at some random point, with all subsequent observations missing. Simulations show that this method of incorporating missing data is conservative and that a target sample size of 70 participants when accounting for up to 15% data missing has a type I error sufficiently close to 5% and power approximately equal to 80%.

Finally, the analysis presented above uses patient-level series. We expect power to increase in our trial analysis because we will analyse series at the eye level. Analysing by eye yields approximately double the number of series. However, the series within patients will be highly correlated, so the effective sample size will be less than double the number of participants.^36^

#### Primary outcome analysis

The primary outcome will be analysed according to the intention-to-treat principle and longitudinal analysis of patients’ progression of VA loss between evaluations at baseline and after 36 months of treatment measured.

We expect VA loss to progress linearly in time for both placebo and VPA-treated participants, on average, although at different rates. We depart from the analysis above by proposing to analyse the series in eyes separately, corrected with glasses, nested within patient. Thus, we initially propose random intercepts for individuals and for eyes within individuals. The patient-level intercept will address the tendency for the vision in the eyes of individual patients to be highly correlated. Additionally, we expect random gradients to be necessary at the eye level to allow that each eye may have its own rate of progression.

Our proposed initial model to analyse VA is:

$$y_{ijk}=\left(\alpha +a_{i}+\;a_{ik}\right)+\left(\beta +\gamma z_{j}+b_{ik}\right)t_{j}+\;\epsilon_{ijk},\;\;i=1,\ldots ,N,\;j=0,\ldots ,6,\;k=0,1$$

Let *i* index patients, so that *i*=1, …, *N*, where *N* is the total trial sample size. Let *t*=*t_VA_* and *j* index *t*, so that *t_0_*=0 and *t_6_*=3 years, etc. Finally, let *k*=0 denote the left eye, and *k*=1 denote the right eye. Let *y_ijk_* denote VA for patient *i* at time *t_j_* in eye *k*. Let *z_i_* take the value 1 if patient *i* is allocated to VPA, else 0.

This model will be fitted in R using the packages nlme or lme4, using restricted maximum-likelihood (REML). General positive-definite covariance structure will be used.

This model assumes that: the patient random intercepts $a_{i}$ are independent for different *i*; the eye random intercepts $a_{ik}$ and slopes $b_{ik}$ are independent for different *i* and *k;* and the within-group errors $\epsilon_{ijk}$ are independent for different *i*, *j* and *k* and independent of the random effects.

Here, α is the fitted mean VA value at *t*=0, β is the mean progression in VA per annum for participants on placebo and γ is the adjustment to the mean progression in VA for participants on VPA, a term we will refer to as the treatment effect.

The sign of γ tells us about the direction of the treatment effect. Negative values represent benefit. The presence or absence of a treatment effect that is unlikely to have occurred through random variation alone will be tested via t-test of the γ-coefficient in the REML fit of the hierarchical model, as recommended by Pinheiro and Bates.^37^

If this model does not fit the observed data satisfactorily, alternative models will be considered.

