### Trial status

Recruitment into the TREATWOLFRAM clinical trial opened in January 2019 and completed in October 2021, with 63 participants (90% of target enrolment) randomised from the six trial sites (University Hospitals Birmingham, UK 11; Birmingham Women’s and Children’s Hospital, UK 14; Almeria, Spain 18; Lodz, Poland 5; Montpellier, France 5; Paris, France 10). This number is seven fewer than planned to allow the trial to complete in a reasonable time. We calculated the minimum number of participants required to achieve 80% power while retaining an acceptable type 1 error. Accepting a type 1 error of 10%, we should still be able to achieve 80% power with 63 participants, while allowing for up to 20% attrition. Online supplemental appendix 8 summarises the recruitment rate. Treatment follow-up and data collection are ongoing, and the last trial visit will take place in November 2024. A summary of the protocol amendments is provided in online supplemental appendix 9.

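### The initial primary model has no patient-level random slope, so if the two eyes of a patient decline at similar rates the test of the treatment effect is anti-conservative

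*Protocol article*

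**What the plan says.** Under Primary outcome analysis, the Protocol article models LogMAR for patient i, visit j and eye k. It begins with intercepts: "Thus, we initially propose random intercepts for individuals and for eyes within individuals". The patient intercept is given the job of handling the similarity of a patient's two eyes. The slope terms follow: "Additionally, we expect random gradients to be necessary at the eye level to allow that each eye may have its own rate of progression". The printed equation accordingly contains a patient intercept a_i, an eye intercept a_ik and an eye slope b_ik, but no patient slope b_i. The assumptions listed below it make b_ik independent across both patients and eyes. The treatment effect γ is the difference in annual progression between arms, tested by a t-test in the REML fit.

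Under Sample size, the article explains that the power calculation used one series per patient, with a random gradient of SD 0.036. It expects eye-level analysis to add power, but cautions that "the series within patients will be highly correlated, so the effective sample size will be less than double the number of participants".

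The planned level is 5% ("Using hierarchical repeated measures analyses with a 5% significance level, 80% power and accounting for an estimated 15% missing data rate"). Under Trial status the article adds, for the number actually randomised: "Accepting a type 1 error of 10%, we should still be able to achieve 80% power with 63 participants".

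**The concern.** A shared intercept lets both eyes of a patient start at a similar level. It does not let them worsen at a similar rate, and the rate is what γ measures. Because treatment is assigned to the patient, any patient-level variation in slope is variation between randomised units and belongs in the standard error of γ. The stated model has no place for it. The general covariance structure does not help: at eye level it can link a_ik with b_ik within one eye, and at patient level there is only a single intercept.

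The article's own premises point the other way. Its planning model has a patient-level gradient, and it expects strong correlation between the two series of a patient. At stake is the primary test of a trial that the article describes as pivotal, and any error runs towards false evidence of efficacy and intervals that are too narrow.

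**Working it through.** **Inputs from the article**
- Slope SD 0.036 and error SD 0.074 (Sample size).
- Visits at 0, 0.5, …, 3 years (Primary outcome measure). The sum of squares of time about its mean is Sxx = 2 × (1.5² + 1² + 0.5²) = 7.
- Allocation 2:1 by patient (Randomisation) and 63 randomised (Trial status).

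**Assumptions**
- The between-eye slope correlation ρ is not given, so the full range 0 to 1 is shown.
- Both eyes are followed, with errors independent between eyes as the model states, and tests are two-sided.
- The 1,500-trial simulations used intercept SDs of 0.35 (patient) and 0.12 (eye).

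**The plan's own figure.** The per-patient slope variance is 0.036² + 0.074²/7 = 0.001296 + 0.000782 = 0.002078. For a difference of 0.041, 5% two-sided, 80% power and 2:1 allocation, the standard random-slope formula gives N = 45, or 53 after dividing by 0.85. The stated 70 is not reproduced. A slope SD of about 0.045 would give 60, or 71 after inflation. The article says that a larger SD was examined but does not print it. This is a separate matter and does not affect the point here.

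**Effect of omitting the patient slope.** Per patient, the mean of two eye slopes has variance
- under the stated model: (0.001296 + 0.000782)/2 = 0.001039;
- with slope correlation ρ: [0.001296(1 + ρ) + 0.000782]/2.

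The ratio is 1 + ρ × 0.001296/0.002078 = 1 + 0.624ρ. The reported SE is too small by the square root of this, and the actual type I error is 2[1 − Φ(1.96/√ratio)], with 1.645 in place of 1.96 at nominal 10%. For ρ = 0.5: ratio 1.312, SE ratio 1.15, error 2[1 − Φ(1.71)] = 8.7%.

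| ρ | Variance ratio | SE ratio | Formula, nominal 5% | Formula, nominal 10% | REML simulation, N = 63, nominal 5% |
|---|---|---|---|---|---|
| 0 | 1.00 | 1.00 | 5.0% | 10.0% | 6–6.5% |
| 0.3 | 1.19 | 1.09 | 7.2% | 13.1% | 7–8% |
| 0.5 | 1.31 | 1.15 | 8.7% | 15.1% | 8.5–9% |
| 0.8 | 1.50 | 1.22 | 10.9% | 17.9% | 10–11% |
| 1 | 1.62 | 1.27 | 12.4% | 19.7% | 12–13% |

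The last column comes from 1,200 simulated null trials per value, fitting the model as printed.

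**Other simulations (nominal 5% unless stated)**
- N = 70, 1,500 trials each: 5.8%, 8.3%, 9.0%, 12.2% and 12.9% at ρ = 0, 0.3, 0.5, 0.8 and 1; 11.3% at ρ = 0.8 with 15% of data missing.
- N = 63, 1,500 trials each: 8.9% at ρ = 0.5 and 14.2% at ρ = 1. At nominal 10% these became 16.1% and 20.9%.
- N = 63, 500 trials each, lower but less precise: 7.6% at ρ = 0.5 and 9.8% at ρ = 0.8.

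**Sensitivity to the slope SD (formula).** The 0.036 was estimated on patient-level series. If it is the patient component and eye variance is added to it, the error is 8.0%, 9.6%, 11.4% and 12.4% at ρ = 0.3, 0.5, 0.8 and 1. With a total eye-slope SD of 0.045 it is 9.3%, 11.9% and 13.5% at 0.5, 0.8 and 1.

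**With a patient slope added.** Over the 1,500-trial scenarios, including ρ = 0, the error was 5.1–5.8% using t with N − 2 degrees of freedom and 5.5–6.3% using a normal reference.

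**Power under the corrected model.** The per-patient slope variance is 0.00208 for one series, and 0.00136, 0.00156 and 0.00169 for two eyes at ρ = 0.5, 0.8 and 1. A real gain remains at every value, smaller than the halving to 0.00104 that the stated model assumes.

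**The case against.** **The correlation is about vision, not rates of loss.** The article speaks of correlated series and correlated vision and assigns that to the intercept. It never says that rates of loss are strongly correlated between eyes. This stands. A reader might infer that the type I error simply is 9–13%, but the document does not support that: the figure requires a slope correlation of about 0.5 or more. A patient-level planning gradient makes a correlation well above zero plausible, but does not fix its size.

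**The model is only initial.** The article calls it so and allows other models if the fit is unsatisfactory. In a simulation with N = 63, a likelihood-ratio comparison with the model containing b_i detected the omission in 26%, 61% and 97% of trials at ρ = 0.3, 0.5 and 0.8. Switching on that result gave type I error of 6.0%, 4.4% and 6.0%. A check of this kind would therefore remove most of the fault, and its details may sit in an analysis plan that is not shown. However, this is the only model the article prints, the fallback names neither a patient slope nor a criterion, and the Masking section says the trial statistician is unblinded. Pre-specifying the term is better than finding it afterwards.

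**The planning simulations showed an error close to 5%.** They used patient-level series, so they do not validate the eye-level model.

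**Fewer than 126 eye series.** Eligibility needs only one eye at 1.6 or better, and off-chart methods are not used in the primary analysis. Patients contributing one eye dilute the inflation, though modestly.

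**Conclusion.** The concern holds in conditional form. As printed, the model understates the standard error of γ whenever rates of loss are positively correlated between a patient's eyes. At nominal 5% with 63 patients, type I error is about 7–8%, 9%, 11% and 12–13% at slope correlations of 0.3, 0.5, 0.8 and 1. At nominal 10% it is about 15–21% for correlations of 0.5 to 1. At zero correlation there is little or no inflation. These figures rest on the article's planning SDs applied to each eye, two eyes per patient and assumed intercept SDs.

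Two stronger readings are tempting but unsupported:
- That a positive result could not be relied on. The design and data are unaffected, and refitting takes one line. On the formula, a nominal p below about 0.025 (ρ = 0.5) or 0.0125 (ρ = 1) would remain significant at 5% after correction.
- That the statement on extra power from eye-level analysis is wrong. The corrected model still gives a gain, and the sample size of 70 does not draw on it.

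**What to change.** Pre-specify a patient-level random slope, with its covariance with the patient intercept, and keep the eye-level terms:

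y_ijk = (α + a_i + a_ik) + (β + γz_i + b_i + b_ik)t_j + ε_ijk

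Test γ with patient-level degrees of freedom (about 63 − 2 = 61). The article does not say which it would use, and the simulations show that this matters much less than the missing slope. Keep the statement that eye-level analysis adds some power, but base any quantified gain on the corrected model.

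The cost is one term in the equation and in the R formula, with no new data. The standard error will be larger where rates of loss are shared between eyes, which is correct. If they turn out not to be shared, little is lost: the simulated error at ρ = 0 with the added term was 5.1%.
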